# Effectiveness of Composite Ayurveda Regimen in a Black Box Design for the Management of Rheumatoid Arthritis: Protocol of a Single Arm, Community-Based Study

**DOI:** 10.2196/57918

**Published:** 2025-02-18

**Keywords:** rheumatoid arthritis, Amavata, Ayush-SG (coded drug), Rasnasaptak Kashaya

## Abstract

**Background:**

Rheumatoid arthritis (RA) is an autoimmune disease that affects joints and can have extra-articular manifestations. RA usually tends to be progressive and leads to substantial health care burdens, both in terms of disability and economic costs. Despite the various treatment modalities available, there is still an urgent need for safe and effective medicine based on the pattern of disease presentation. The increasing interest in complementary and alternative medicine has created a demand for extensive research in this area.

**Objective:**

This clinical study is designed to evaluate the effectiveness and tolerability of a composite Ayurveda regimen in RA.

**Methods:**

The study is a single-arm (pre-post design), community-based interventional study with a black box design being conducted at 6 study centers. A total of 240 participants aged between 18 and 65 years, diagnosed with RA as per the 2010 American College of Rheumatology and the European League Against Rheumatism criteria are recruited as per the selection criteria. All the participants received Ayush-SG and *Rasnasaptak Kashaya* for 84 days along with customized treatment as per the disease presentation and associated complaints. The outcome measures include the change in disease activity score (DAS)-28 with erythrocyte sedimentation rate, disease-specific biochemical and inflammatory markers, Disability Index score, change in the participant’s assessment of pain and frequency of use of conventional analgesics or nonsteroidal anti-inflammatory drugs from baseline. The tolerability of interventions is assessed through the occurrence of adverse events. Categorical variables will be analyzed with McNemar chi-square test, and continuous variables will be assessed using the paired *t* test or Wilcoxon test for pre-post assessment. The level of significance will be 5%.

**Results:**

The recruitment of participants was initiated in December 2023. The participant recruitment was completed in March 2024 and out of 240 participants enrolled, 222 (92.5%) completed the study up to the last follow-up. Data verification, compilation, and analysis are under process. After data analysis, the study’s findings will be published in a peer-reviewed journal.

**Conclusions:**

This interventional study that incorporates the black box approach may provide a strong framework for managing RA. This design is a more reliable method for evaluating the effectiveness and tolerability of the composite Ayurveda regimen in RA.

**Trial Registration:**

Clinical Trial Registry-India CTRI/2023/06/054203; https://tinyurl.com/4prvwr6z

**International Registered Report Identifier (IRRID):**

DERR1-10.2196/57918

## Introduction

### Background

Rheumatoid arthritis (RA) is a chronic inflammatory autoimmune disease that can damage joints and affect extra-articular organs. In 2019, 18 million people worldwide were living with RA. Women accounted for 70% of cases, and over half were older than 55 years [1]. The articular manifestation of RA includes symptoms such as musculoskeletal pain, swelling, and stiffness of joints. It is usually symmetric and initially manifests in small joints and progresses to larger joints. Over time, joint inflammation can lead to joint destruction, including loss of cartilage and bone erosion [2]. The symptoms of RA vary in patients; some patients have mild self-limited disease, while many experience joint destruction, severe physical disability, and multiple comorbidities. RA tends to be progressive in nature, involving a worsening of symptoms over time, and often begins for many people during the early or middle years of life, thus causing a heavy burden on society in terms of disability, health, and economic costs. The available evidence for pain management in RA involves the use of disease-modifying antirheumatic drugs and medications such as nonsteroidal anti-inflammatory drugs (NSAIDs) which play an important role in its management but may suppress the immune system and, lead to an increased risk of infections as well other side effects as gastrointestinal disturbances [3,4]. People from all over the world are also developing an interest in traditional herbal practices. It is reported that 60% to 90% of persons with arthritic conditions use complementary and alternative medicines [5-7]. In a study conducted in the United States, it was reported that around 60% of persons with arthritic conditions including RA use complementary and alternative medicines. Of these, 28% reported a history of herbal therapies, and 22% used diet supplements [8].

RA resembles the condition “*Amavata”* (rheumatism due to Ama) described in Ayurveda*,* where both the *Ama* (undigested or intermediate product of digestion or metabolism that act as a toxin in the body) and *Vata Dosha* (*Dosha* responsible for movement and cognition) become vitiated and located in the *Sandhi* (joints) leading to pain and inflammation in the joints. The causative factors of Amavata are described as *Viruddha Ahaara* (antagonistic food), *Viruddha Vihaara* (antagonistic lifestyle), *Mandagni* (subdued digestive power), a sedentary lifestyle, and exercising immediately after meals. Long-term adherence to these etiological factors causes vitiation of *Vata* along with impaired digestion and metabolism in the body leading to the formation of *Ama*. The gradual accumulation of *Ama* obstructs different *Srotas* (structural or functional channels) in the body and further vitiation of *Tridoshas* (3 regulatory functional factors of the body). The Ama and Vata along with other vitiated Doshas lead to the impairment of *Dhatus* (major structural components of the body) mainly joints causing the *Amavata* [9].

The Ayurvedic classics describe various treatment modalities and therapeutic formulations based on the condition and clinical presentation of the disease. The disease pattern of *Amavata* in a person depends on the extent of *Ama* association, *Dosha* vitiation, and the chronicity of the condition. In cases of *Amavata* with significant *Ama* association, there may be obstructions in the *Srotas*, leading to symptoms like severe pain, swelling, elevated temperature, and redness in the joints. The treatment for this scenario should prioritize digesting *Ama* and clearing the obstructions in the *Srotas* along with alleviation of vitiated *Dosha*. If there is only mild *Ama* association and less *Dosha* imbalance, symptoms may be limited to joint pain, stiffness, and minimal swelling, indicating medications that digest *Ama* and alleviate *Doshas* predominantly *Vata*. In chronic cases, patients may experience symptoms like mild aching stiffness, fatigue, or anemia. The choice of medicines varies according to each pattern of presentation and must be determined by the practitioner following a thorough assessment of the patient’s condition. In a standard randomized controlled trial (RCT), it is not feasible to design a customized regimen that tailors medicine selection to specific conditions. In such instances, a specialized trial design should be considered to facilitate the prescription of medicines tailored to the clinical manifestations and disease stage of each individual. To address this issue, it is essential to consider modifying study designs, including exploring alternative approaches such as “black-box” designs [10].

The treatment plan for *Amavata* is focused on the digestion of *Ama* and the alleviation of *Vata*. For digesting the *Ama* and removing obstruction from the *Srotas*, drugs having *Katu* and *Tikta* Rasa (pungent and bitter tastes), *Pachana* (enhancing digestion), and *Dipana* (enhancing metabolic fire) properties have to be administered [11]. Ayush-SG, *Rasnasaptak Kashaya*, and *Guduci* (*Tinospora cordifolia*) have the above-said properties. Ayush-SG is a coded drug developed by the Central Council for Research in Ayurvedic Sciences (CCRAS) for the management of Amavata [12]. *Rasnasaptak Kashaya* is described in the context of *Amavata* treatment in Ayurveda classics [13]. *Brihat Saindhawadi Taila* and *Dashang Lepa* are used for local application to pacify pain and inflammation of the joints [14-16]. Considering the major patterns of disease presentations, a black box design has been planned for this study and the treatment has been tailored according to the accompanying symptoms.

### Objectives

The primary objective of the study is to evaluate the effectiveness of a composite Ayurveda regimen on the disease activity score (DAS) in RA.

The secondary objective is to evaluate the effectiveness of the composite Ayurveda regimen on the disease-specific biochemical and inflammatory markers and assess the tolerability of Ayurveda regimen in RA.

## Methods

### Study Design

This is a single-arm (pre-post design), community-based interventional study with a black-box research design.

### Study Setting

The study is conducted through 6 research institutes under CCRAS at New Delhi, Patiala, Guwahati, Gwalior, Vijayawada, and Chennai in identified areas predominantly dwelled by the scheduled caste population near the institute.

### Inclusion Criteria

Participants aged between 18 and 65 years, diagnosed with RA as per the 2010 American College of Rheumatology and the European League Against Rheumatism criteria [17], and willing to give written informed consent for participation are enrolled in the study.

### Exclusion Criteria

Participants presenting with complications of RA, for example, deformity of joints/bones, pleura-pericardial disease, participants with extra-articular manifestations of RA and gastrointestinal symptoms, those with joint prosthesis or unable to walk without support or confined to a wheelchair, participants with Hemoglobin <8 g/dL, diagnosed with other arthritis like osteoarthritis, gouty arthritis, tuberculous arthritis, psoriatic arthritis, spondyloarthropathy, active fibromyalgia, juvenile chronic arthritis, ulcerative colitis, or other systemic inflammatory conditions and autoimmune diseases, having blood pressure ≥ 160/100 mm Hg, or hemoglobin A_1c_ (HbA_1c_)>8%, on medication with corticosteroids, antidepressants, anticholinergics, etc or Ayush interventions/folk medicine or any other drugs that may influence the outcome of the study are excluded from the study. Participants with diagnosed concurrent neurological, pulmonary, or endocrine disorder, or unstable cardiovascular disease, with concurrent serious hepatic disorder (defined as aspartate aminotransferase or alanine aminotransferase, total bilirubin, alkaline phosphatase > 2 times upper normal limit) or renal disorders (defined as S Creatinine > upper normal limit); participants with alcohol use disorder (CAGE score >2) or any other substance abuse; and pregnant or lactating woman are not enrolled in the study.

### Study Procedure

The participants have been screened from the out-patient departments, camps, or door-to-door visits in the identified areas. Before the initiation of the study, the head of the village or local administrative authority and the residents of the area were informed about the study in detail, in their regional language. Participants diagnosed with RA have been enrolled based on the defined inclusion and exclusion criteria.

Laboratory investigations such as complete blood count with an erythrocyte sedimentation rate (ESR), liver function test, renal function test, and C-reactive protein, RA factor (quantitative), serum immunoglobulin G, and serum immunoglobulin M have been conducted at baseline and the end of the treatment (84th day). HbA_1c_ levels are determined at baseline only (Figure 1)**.**

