### Withdrawal Criteria

The participant has been withdrawn from the study if they have not been willing to continue, if there has been a worsening of RA symptoms, or if they have developed any other illness mentioned in the exclusion criteria. The decision to withdraw a participant from the study has been made solely by the Investigator, who has then had to provide a detailed justification and indicate the line of further management if needed.

In the case of any adverse event, serious adverse event, or adverse drug reaction, the Institutional Ethics Committee (IEC) and Data Safety Monitoring Board are to be informed and participants are to be withdrawn from the study.

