### Outcome Measures

The primary outcome of the study is the change in the DAS-28 score (with ESR) [18] and it is assessed at baseline and the end of the treatment (84th day). Secondary outcomes include the change in disease-specific biochemical and inflammatory markers (RA factor, C-reactive protein, and ESR) and serum immunoglobulin levels (Immunoglobulin G and Immunoglobulin M), participants’ assessment of Pain, Global assessment of disease activity, change in Disability Index score and frequency of use of conventional analgesic/NSAIDs medicines and occurrence of adverse events if any. The change in disease-specific biochemical and inflammatory markers and serum immunoglobulin levels are assessed at baseline and on the 84th day. The participants’ assessments for pain and global assessment of disease activity are assessed using the visual analog scale [19] ranging from 0 mm (no pain) to 100 mm (worst possible pain) at baseline, 28th day, 56th day, and 84th day. The change in Disability Index score is assessed using the Indian Health Assessment Questionnaire [20] at baseline, 28th day, 56th day, and 84th day. The frequency of use of conventional analgesic/NSAIDs medicines and occurrence of adverse events are also assessed in a time frame of baseline, 28th day, 56th day, and 84th day (Figure 1).

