### Statistical Analysis

After data collection, verification of its accuracy and limits will be done. The filtered data will be used for additional analysis and interpretation. The Categorical variables will be reported in number (percentage) and analysis of pre-post-trial outcomes will be done by the Mc-Nemar chi-square test. The continuous variables (like scores and lab parameters) will be analyzed by paired *t* test/Wilcoxon test as per the distribution of data in the pre-post trial situation. The assessment parameters assigned in more than 2 follow-ups will be analyzed using the r-ANOVA/Friedman test/ Cochran Q test. The continuous data having normal distribution will be represented as mean (SD) and the data not having normal distribution as median (IQR). The 5% level of significance will be used throughout the analysis. The SPSS (version 26.0; IBM Corp) software will be used to conduct the analysis.

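### Liver and renal tests are collected but left out of tolerability, and the paired test of average change named for laboratory data can miss a handful of marked individual rises

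*Protocol article*

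**What the plan says.** - **What is measured.** Study Procedure puts "liver function test, renal function test, and C-reactive protein" in a panel of tests that "have been conducted at baseline and the end of the treatment (84th day". No laboratory visit is shown at day 28 or day 56.
- **What counts as tolerability.** Tolerability is part of the secondary objective. The Abstract states: "The tolerability of interventions is assessed through the occurrence of adverse events". Under Outcome Measures, the "occurrence of adverse events are also assessed in a time frame of baseline, 28th day, 56th day, and 84th day".
- **Which laboratory values are outcomes.** Outcome Measures lists the "change in disease-specific biochemical and inflammatory markers (RA factor, C-reactive protein, and ESR) and serum immunoglobulin levels". Liver and renal function are not named.
- **How laboratory values are analysed.** Statistical Analysis says "The continuous variables (like scores and lab parameters) will be analyzed by paired" t test or Wilcoxon test, chosen by distribution. Categorical variables are given as numbers and percentages with a McNemar test, but no liver or renal category is named.
- **Individual limits.** These appear only in the Exclusion Criteria: for liver tests, values including "total bilirubin, alkaline phosphatase > 2 times upper normal limit"; for renal disorder, creatinine above the upper limit.
- **Withdrawal.** Withdrawal Criteria removes anyone who develops an illness named in the exclusions. It adds that after any adverse event "participants are to be withdrawn from the study".

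**The concern.** Drug effects on the liver or kidney typically show as large changes in a few people, not as a small shift in everyone. A paired test of average change is built for the second pattern. The trial holds before-and-after liver and renal results, but the article names only that test for laboratory parameters and leaves these tests out of the tolerability outcome.

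The risk is a report in which mean enzyme and creatinine changes are non-significant, few adverse events were recorded, and the regimen is called well tolerated, although several participants ended treatment with markedly abnormal results and no symptoms. Selection adds to this. If the withdrawal rule for adverse events was followed, the day-84 panel comes mainly from participants without an earlier adverse event.

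**Working it through.** **The article's own figures.** 6 centres × 40 = 240 enrolled; 222/240 = 92.5% completed; 240 − 222 = 18 (7.5%) did not. There is no power calculation to reproduce, because the sample size rests on feasibility.

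**1. Wilcoxon signed-rank test, n = 222 pairs.** Assume that k participants have the k largest changes, all upward, and that the rest vary symmetrically around zero. Under no effect, the rank sum has mean 222 × 223/4 = 12,376.5 and SD √(222 × 223 × 445/24) = 958. The k top ranks move the rank sum by half their total.

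| k | Sum of top k ranks | Shift in z = (sum/2)/958 | Approx. chance of p < 0.05 |
|---|---|---|---|
| 2 | 443 | 0.23 | 6% |
| 4 | 882 | 0.46 | 8% |
| 6 | 1,317 | 0.69 | 11% |
| 8 | 1,748 | 0.91 | 15% |
| 18 | 3,843 | 2.01 | 52% |

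The last column is P(Z > 1.96 − shift) + P(Z < −1.96 − shift). Only ranks count, so the size of the rises does not matter once they are the largest changes. About 18 of 222 (8.1%) are needed for an even chance of significance.

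**2. Paired t test.** If k participants rise by the same amount D and the others do not change, then t = √[k(n − 1)/(n − k)], whatever D is, because D inflates the SD along with the mean. Unequal rises give a smaller t. The two-sided 5% critical value on 221 df is 1.97.

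- k = 2: √(2 × 221/220) = 1.42
- k = 3: √(3 × 221/219) = 1.74
- k = 4: √(4 × 221/218) = 2.01
- k = 6: √(6 × 221/216) = 2.48

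Two or three rises, however large, fall short unless chance variation in the others tips the result. Four sit on the border.

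**3. Simulations.** The article gives no enzyme values, so every input here is an assumption.

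*Set A:* 222 pairs, log-normal, median 0.55 × the upper limit, log-scale SD 0.35 between and 0.18 within persons; k participants end at 3 to 6 × the limit; 3,000 runs.

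| k | t test significant | Wilcoxon significant |
|---|---|---|
| 2 | 3.5% | 4.7% |
| 4 | 38% | 6.6% |
| 6 | 93% | 9.8% |

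With k = 4 the mean moves by only 0.07 × the limit.

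*Set B:* affected participants rise by about 125 U/L (SD 20); the others change by a mean of 0, −1 or −2 U/L with SD 8 or 12; 4,000 runs. Ranges cover these settings, and only significant rises are counted.

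| k | Mean change (U/L) | t test | Wilcoxon |
|---|---|---|---|
| 2 | −0.9 to +1.2 | 0–9% | 0–4% |
| 5 | +0.9 to +2.8 | 0–59% | 0–8% |
| 8 | +2.6 to +4.5 | 8–99% | 0–14% |

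A slight average improvement in the unaffected can cancel the signal from the affected.

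**4. What counts would show from the same samples.** Exact 95% CIs: 2/222 = 0.9% (0.1 to 3.2%); 5/222 = 2.3% (0.7 to 5.2%); 8/222 = 3.6% (1.6 to 7.0%). For 0/222 the two-sided upper limit is 1 − 0.025^(1/222) = 1.6%. These describe only those tested.

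**The case against.** The strongest reply is that no passage ties the tolerability conclusion to the paired laboratory test. Adverse events are assessed per participant at days 28, 56 and 84, symptoms are recorded at each follow-up, and events go to the ethics committee and the safety board. The power of a paired test is therefore not the power of the tolerability assessment. This stands for symptomatic toxicity. A day-84 abnormality could also be recorded as an adverse event, and nothing in the article excludes that; equally, nothing shown requires it.

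Second, the McNemar test could be applied to normal versus abnormal results. The article names no such category. Anyone above the entry limits was also excluded, so all changes across those limits would be new abnormalities, and the uncorrected chi-square would equal their number k. With fewer than four it stays below 3.84. The count itself is the useful result, not the test.

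Third, shift tables and rules for abnormal results commonly sit in an analysis plan that is not shown. Their absence is not the point here. The point is that the one method the article does name for laboratory parameters suits individual safety data poorly.

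Fourth, the enzyme inputs are assumed, and the t test does detect larger clusters: 93% of runs with six rises in set A. That is correct, and it limits the claim.

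**Conclusion.** The point holds in a limited form. Asymptomatic liver or kidney abnormalities that are not recorded as adverse events could be missed. A non-significant average change would be no evidence against them.

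The Wilcoxon result depends little on the assumed enzyme values. It needs only that the affected participants have the largest changes and that the rest show no systematic change; on that basis the chance of significance is about 15% or less for up to eight rises. The t test is weak for two or three rises, variable at four or five, and usually sensitive at six or more, unless the other participants improve slightly on average.

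A reader might infer that toxicity would be hidden, or that the 18 non-completers disappear from view. The documents do not support either. Adverse events are counted individually, and reasons for withdrawal or dropout are recorded in the case record form. Nor does the article say whether an exit sample was taken, so the number without a day-84 panel is unknown. A true frequency of 7.5% would require all 18 non-completers and none of the 222 to be affected; that is an extreme bound, not an estimate.

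Separately, Withdrawal Criteria relies on liver and renal conditions defined by laboratory limits, while Study Procedure shows no scheduled laboratory test between baseline and day 84 that could reveal them. These sections need to be reconciled.

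**What to change.** No further blood tests are needed, and the article says analysis is still under way.

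1. Name liver and renal function under tolerability in Outcome Measures, alongside adverse events.
2. In Statistical Analysis, report baseline-to-day-84 shift tables for these tests. Give the number and percentage of participants newly above the limits already in the Exclusion Criteria (liver tests more than 2 times the upper limit, creatinine above the upper limit), with exact 95% CIs.
3. State how many of the 240 have no day-84 sample and why, and confine laboratory-tolerability statements to those tested.
4. State that the paired t or Wilcoxon test will not be used as evidence of laboratory safety.
5. Reconcile the withdrawal provision for illnesses in the exclusions with the laboratory schedule, by describing how it was applied during follow-up.

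The cost is a few tables from data already collected. The downside for the sponsor is a possibly less favourable tolerability statement.
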